### Study implementation

This is an ongoing study. All recruitment, enrollment and data collection are expected to take place over an 18-month period.

#### Participant recruitment and enrollment (January – June 2024)

After the client receives their contraceptive method of choice, health workers will provide each client receiving injectables with information about the study, inquire about interest/willingness to learn more about the study, and—if she agrees—obtain informed consent and record her contact information in an enrollment log. Clients providing informed consent to be contacted by study team members will be asked how they would like to be contacted (via telephone or home visit) and contact information recorded. At the end of each workday, health workers will then share enrollment details with study staff, who will contact the client in-person or by phone to confirm eligibility and consent and conduct intake interviews.

Enrollment limits proportional to average family planning client caseload will be set for each facility type, to ensure cohorts include participants from all levels of the health system.

#### Data collection instruments and procedures

Data collection instruments are available in Additional file 2.

### Cohort intake (Tool A) and follow-up (Tool B)

Structured intake interviews will be conducted within two weeks of enrollment. For participants indicating a preference for telephone contact, up to three attempts will be made to make each contact. Participants who indicated a preference for conducting interviews in person, as well as those that could not be reached via telephone and consented to home visits if needed, will be visited at home. Up to three attempts will be made to find a participant in their community. If participants cannot be reached after three attempts via telephone and/or three attempts in person, they will be considered ‘lost to follow up’ and dropped from the study cohort.

Approximately 120–130 days following the date each participant received/administered their contraceptive injection at the health facility and enrolled in the study, participants will be contacted for a follow-up interview (interview #2) using Tool B. This window reflects the expected period of time by which a subsequent injection would have taken place, if conducted within the effective window for DMPA (up to two weeks earlier or four weeks later than the targeted three-month reinjection date), During each follow-up interview, participants will be asked if they received (DMPA-IM) or received/administered another contraceptive injection (DMPA-SC) within the last month. If yes, the study staff will document the date the injection occurred and proceed with the interview on their experiences. If no, the study staff will proceed with questions on discontinuation, and the participant will be dropped from the study cohort.

Approximately 120–130 days following the date each participant reported receiving/administering a second contraceptive injection, they will be contacted for another follow-up interview (interview #3) and the same procedures followed. Similarly, approximately 120–130 days following the date each participant reported receiving/administering a third contraceptive injection, they will be contacted for a final follow-up interview (interview #4) and the same procedures followed. At the end of the interview, participants will be thanked for their participation and informed that the study is completed, and they will not be contacted again.

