## Background

Depot medroxyprogesterone acetate (DMPA) is a highly effective family planning method that requires administration every three months for continued contraceptive protection [1]. Recent estimates suggest that injectables are currently used by more than 72 million women worldwide and, while injectables are the most common modern contraceptive method in sub-Saharan Africa, they are less common in other geographic regions [2]. However, science is continuously evolving; continued investments in contraceptive technology have led to emergence of new contraceptive methods, formulations and designs with the aim of improving availability and accessibility of contraceptive choices that meet the needs of women and men around the world [3]. Among these advancements is the introduction of a subcutaneous formulation of DMPA (DMPA-SC), which is therapeutically equivalent and has a similar safety profile as the syringe-administered intramuscular formulation (DMPA-IM) but is administered through the Uniject system with a smaller needle and slightly lower hormonal dose [4].

In recent years, evidence has demonstrated that self-injection of DMPA-SC is safe, feasible, acceptable, can lengthen method continuation, and expands contraceptive accessibility to groups with lower health service utilization rates [5]. For example, a 2019 meta-analysis found higher rates of continuation with self-administration of injectable contraception compared to provider administration, and found no difference in reported pregnancies across arms [6]. World Health Organization (WHO) guidelines for sexual and reproductive health self-care interventions promote scale-up of self-administered DMPA-SC as part of strategies to reduce unmet need for contraception and achieve universal access to sexual and reproductive health [7], and there are numerous governments, foundations and civil society organizations around the world involved in DMPA-SC introduction efforts [8].

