#### Criteria for discontinuation of a participant

Consistent with DMPA-SC cohort studies conducted in other low-and-middle income countries, contraceptive discontinuation will be defined as women who did not obtain a scheduled injection, or who self-injected or received any injectable contraceptive more than 120 days after the previous injection. If a participant chooses to discontinue use of contraception or switch to another contraceptive method (either injectable or non-injectable), they will be removed from the study cohort. Participants may also choose to withdraw from participation in the study at any time, with no impact on their access to family planning services.

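### The follow-up question looks back one month from day 120–130, so women who reinjected early, and most who reinjected on the target date, answer no and are dropped

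*Protocol article*

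**What the plan says.** The section on cohort intake and follow-up (Tools A and B) fixes four things.

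- **Timing.** The first follow-up interview comes "Approximately 120–130 days following the date each participant received/administered their contraceptive injection at the health facility and enrolled in the study". Interviews #3 and #4 are timed the same way from the second and third injections.
- **Reason for the timing.** By then the effective window should have closed, that window being "up to two weeks earlier or four weeks later than the targeted three-month reinjection date".
- **Question.** At each follow-up, "participants will be asked if they received (DMPA-IM) or received/administered another contraceptive injection (DMPA-SC) within the last month".
- **Consequence.** A yes leads staff to note when the injection took place and to carry on with the interview. A no ends follow-up, in these words: "If no, the study staff will proceed with questions on discontinuation, and the participant will be dropped from the study cohort".

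The procedure recurs up to the end of follow-up: "they will be contacted for a final follow-up interview (interview #4) and the same procedures followed".

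The section on criteria for discontinuation of a participant sets a different test. Discontinuation there means not obtaining a scheduled injection, or being a woman "who self-injected or received any injectable contraceptive more than 120 days after the previous injection". The same section also removes women who switch method.

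**The concern.** The interview is deliberately late, so that the whole reinjection window has passed, but the recall period is too short to cover that window. The women it misses are the most punctual ones. Someone who reinjected on day 85 is inside the accepted window and is a continuer by the discontinuation definition. Asked on day 120 or later about the last month, she truthfully says no and is removed.

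The injection date is documented only after a yes, so the article describes no record from which the error could later be corrected. The 12-month continuation comparison is the primary objective, and each woman must pass this screen three times to count as continuing.

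The error need not be equal between arms. DMPA-SC users take three units home, whereas DMPA-IM must be given by a health worker, so reinjection timing could plausibly differ. The bias could then create, hide or reverse a difference.

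**Working it through.** **Inputs from the article:** interview on day 120–130 after the previous injection; recall of the last month; window from two weeks before to four weeks after the three-month date; discontinuation if the gap exceeds 120 days; design comparison of 50% against a 10-point difference, 500 per group, 75% retention.

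**Assumptions:** three months = 91 days (90–92 also tried); a month = 30 days (28 and 31 also tried).

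**1. The plan's own figures.** The window is 91 − 14 = day 77 to 91 + 28 = day 119, which is 43 days. It closes just before the 120-day limit and the first interview day, so timing and definition agree with each other. The sample size is also close: 50% against 60%, two-sided 0.05, 80% power, needs 385 evaluable per group (unpooled variance), and 385/0.75 ≈ 514, against the stated 500. The sample size is not in dispute.

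**2. What the question can capture.** A reinjection on day *d* is reported at an interview on day *I* only if *d* ≥ *I* − 30.

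| Interview day | Reaches back to | Accepted days missed |
|---|---|---|
| 120 | day 90 | 77–89: 13 of 43 (30%) |
| 130 | day 100 | 77–99: 23 of 43 (53%) |

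- Days 77–89 are missed at every interview day.
- Day 90 is captured only at a day-120 interview.
- Day 91, the target, is captured on days 120 and 121 and missed on days 122–130, 9 of 11.
- At a day-130 interview, women up to 8 days after the target (day 99) are missed too.

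**3. Sensitivity.** With the target at day 91 and a month of 28 to 31 days, the misses are 15 to 12 of 43 at day 120 and 25 to 22 of 43 at day 130. Over all combinations tried (target day 90–92, month 28–31 days), the target day is captured on 0 to 4 of the 11 interview days.

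**4. Effect on the endpoint (illustration).** The article gives no distribution of reinjection dates, so these are assumed. Interview days are uniform over 120–130, true 12-month continuation is 50%, and the rule is applied literally at three interviews. Apparent continuation = 0.50 × (share captured)³.

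| Assumed reinjection dates | Share captured | Apparent continuation |
|---|---|---|
| Uniform over days 77–119 | 25/43 = 0.581 | 0.50 × 0.581³ ≈ 10% |
| Centred on day 98, SD 7 | 0.675 | 0.50 × 0.675³ ≈ 15% |
| Centred on day 105, SD 7 | 0.912 | 0.50 × 0.912³ ≈ 38% |

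The two normal cases use whole days within the window. Two arms with the same true 50% but centres one week apart would appear to differ by about 38 − 15 = 23 points. With identical timing and equal true rates, no arm difference arises.

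**5. A milder illustration.** Suppose only 10% of true continuers are wrongly dropped at each follow-up. True rates of 50% and 60% become 0.50 × 0.9³ = 36% and 0.60 × 0.9³ = 44%, and power at 375 evaluable per group (500 × 0.75) falls from 0.79 to 0.53. With 10% dropped in the DMPA-IM arm and 20% in the DMPA-SC arm, the rates are 36% and 0.60 × 0.8³ = 31%, and the direction reverses.

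**The case against.** The strongest reply is that the instrument itself is in Additional file 2, which was not available for this review. Tool B may ask about any injection since the previous one, or the discontinuation questions may bring an earlier injection to light. The article also does not say in so many words that a no is coded as the discontinuation event. These points limit what can be claimed about actual practice. They do not rescue the written rule, which states the question, removes the woman on a no, and describes no check for an earlier injection. Coding her as censored rather than as an event would still lose the most punctual users selectively.

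A second reply concerns size. The counts out of 43 are calendar days, not women. The percentages in steps 4 and 5 rest on assumed timing or error rates and literal answers, and the 23-point gap comes entirely from assuming a one-week difference between arms. That stands: those figures show what the rule could do, not what it will do. Neither the size nor the direction of any arm difference is documented.

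Third, interview days are approximate, and a woman who reinjected on target or a day or so before it can be captured by a very early interview. This is correct and is reflected in the counts above. The misses that hold throughout are the earlier reinjections.

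**Conclusion.** The concern holds. The one-month recall contradicts both the reinjection window given in the same section and the discontinuation definition, and it governs who stays in the cohort for the primary outcome. With a 91-day target and a 30-day month, 30% to 53% of the accepted reinjection days yield a false no, and the target day does so on 9 of 11 interview days. Other reasonable month lengths and target days do not change the conclusion. That part rests on the article's dates and simple arithmetic. How far the continuation rates and the arm comparison would be distorted depends on unknown reinjection dates and on how Tool B is actually worded and used.

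**What to change.** - **Question.** In the follow-up section, and in Tool B if it carries the same wording, replace the one-month recall with any injection since the last recorded one, with that date read to the participant.
- **Recording.** Document the date of any such injection for every woman before deciding which branch of the interview she follows.
- **Classification.** Derive continuation from the recorded interval under the existing definition (no more than 120 days, against more than 120 days or no injection), keeping the separate rule on switching in force. Remove a woman from follow-up only on that basis.
- **Women already dropped.** Check whether each no concealed an earlier injection, by re-contact or from data already held, before counting it as a discontinuation. If Tool B already used the wider question, correct the article's text and say so.

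The wording change is one line and adds no visits, and the sample size is unaffected. The real cost is the recheck. Enrollment ran January–June 2024 and data collection was planned for 18 months, so much of the follow-up may be complete. Re-contact would then rely on longer recall, and interviews missed after a wrongful removal may not be recoverable.

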### Sub-study (Tool C)

During interview #3, DMPA-SC users who live in selected tehsils (sub-districts), are participating in telephone interviews and received/administered a third injection during the study period will be asked if a study staff member can visit their home to better understand how they manage storage, self-injection and waste disposal practices. If the participant agrees, a study staff member will visit their house on an agreed date and time. Upon arrival, the data collector will read a brief consent script to remind participants about the scope and voluntary nature of the study. They will then proceed with questions and visual verification of DMPA-SC product storage conditions, ask participants to demonstrate self-injection procedures using a model like that used in training, and to explain/demonstrate waste disposal practices. DMPA-SC users who live in these tehsils and were not reachable via telephone or indicated a preference for in person follow-up will be visited for interview #3 as described above. At the end of the interview, they will be asked if they are willing to answer a few additional questions and show the study staff how they manage storage, self-injection and waste disposal. If participants agree, study staff will proceed with the interview and observation checklist during the same visit.

#### Criteria for discontinuation of a participant

Consistent with DMPA-SC cohort studies conducted in other low-and-middle income countries, contraceptive discontinuation will be defined as women who did not obtain a scheduled injection, or who self-injected or received any injectable contraceptive more than 120 days after the previous injection. If a participant chooses to discontinue use of contraception or switch to another contraceptive method (either injectable or non-injectable), they will be removed from the study cohort. Participants may also choose to withdraw from participation in the study at any time, with no impact on their access to family planning services.

#### Data management and processing

Data collection will be conducted using Research Electronic Data Capture (REDCap) software on tablet or laptop computers. Routine data management and quality checks will be done in Stata version 14 or higher.

#### Data analysis

Characteristics (e.g. demographics, contraceptive history, reasons for methods choice, reproductive empowerment measured using a validated scale developed by MEASURE Evaluation [25], general self-confidence) and experiences of women enrolled in DMPA-SC and DMPA-IM study arms will be compared using *t* tests for continuous variables and chi^2^ tests for categorical variables. Differences in contraceptive continuation rates of DMPA-IM and DMPA-SC users will be compared at each follow-up point (6,9 and 12-month continuation rates) using Kaplan–Meier survival analysis methods and factors associated with risk of discontinuation analyzed using a Fine-Gray subdistribution hazard model.

Additional descriptive analyses of DMPA-SC user characteristics and experiences may include comparisons of the proportion of clients opting for DMPA-SC who successfully self-inject their first dose under the supervision of a provider; if assistance is sought for subsequent injections; what type of assistance is sought, and from who; and confidence in self-injection capacity.

DMPA-SC client adherence to storage, injection timing, and waste disposal standards will also be measured using descriptive statistics, with sub-analyses comparing differences in adherence based on household demographics, location and access to health services.

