**Methods:**

A prospective cohort study will be conducted in 41 health facilities and surrounding communities in Punjab, Pakistan. The primary objective of the study is to compare the 12-month contraceptive continuation rate for women who receive DMPA-SC with that for women who receive intramuscular depot-medroxyprogesterone acetate (DMPA-IM). The secondary objectives are to compare characteristics and experiences of participants who opt for DMPA-SC with those of women who opt for DMPA-IM, which must be administered by a health worker. Additionally, a sub-study is planned to assess how well women opting for self-injection of DMPA-SC adhere to standards for commodity storage, injection timing, injection technique and waste disposal.

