## Methods/design

### Study design

This will be a non-randomized prospective cohort study. We calculated the sample size necessary to detect a 10% difference in 12-month continuation rates between DMPA-SC and DMPA-IM users with 80% power at 0.05 level of statistical significance. Assuming equal preference for each injectable method, a 12-month continuation rate of 50% for DMPA-IM users, and a retention rate of 75% follow-up following the 4th injection (the equivalent of 12-months of contraceptive coverage), a total of 500 participants are needed in each intervention group. Thus, we anticipate enrolling a total of 1,000 women (500 DMPA-SC clients and 500 DMPA-IM clients).

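### Follow-up experiences are asked only of women who report another injection, so the planned comparison between enrolled arms is in fact a comparison among continuers

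*Protocol article*

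**What the plan says.** The Abstract sets a secondary objective to "compare characteristics and experiences of participants who opt for DMPA-SC with those of women who opt for DMPA-IM". The Data analysis section carries this into unadjusted t and chi-square tests: "experiences of women enrolled in DMPA-SC and DMPA-IM study arms will be compared". Both sentences describe women who started a method. Neither restricts the comparison to women who stayed on it.

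The section on cohort intake (Tool A) and follow-up (Tool B) fixes who is asked what.

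- Intake covers all participants: "Structured intake interviews will be conducted within two weeks of enrollment".
- At each follow-up interview, a woman is asked whether she has had another injection. One who has had it gives its date and is then asked about her experiences.
- A different branch applies to the rest: "If no, the study staff will proceed with questions on discontinuation, and the participant will be dropped from the study cohort".

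The criteria for discontinuation apply the same removal to women who stop contraception and to those who "switch to another contraceptive method (either injectable or non-injectable), they will be removed from the study cohort".

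The Study design section powers the study to "detect a 10% difference in 12-month continuation rates between DMPA-SC and DMPA-IM users with 80% power at 0.05 level of statistical significance", from 50% for DMPA-IM.

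**The concern.** As written, experience data at interviews #2, #3 and #4 come from women who reported a further injection, and the group narrows at each round. Reported reinjection is what the primary outcome is built from. The comparison of follow-up experiences is thus made after selection on an outcome that the plan itself expects to differ by arm.

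Experience probably affects continuation. The Background reports that 56% of women who stop a method within 12 months do so for reasons other than wanting a pregnancy, and it names method-related reasons, health concerns, cost and inconvenience. Women with these problems are the ones routed away from the experience questions.

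If one arm keeps more of its dissatisfied women, it looks worse among continuers even when the starters in both arms fared equally. The same selection can hide a real difference. A reader weighing DMPA-SC introduction could take a comparison of continuers for the experience of everyone who chose each method. The primary continuation comparison is not touched by this point.

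**Working it through.** **The plan's own figure.** Inputs from Study design: 50% against 60% (the 10-point difference, taken in favour of DMPA-SC), 80% power, alpha 0.05 (two-sided assumed), 75% retention. Unpooled formula: (0.25 + 0.24) × (1.960 + 0.842)² / 0.10² = 385 per arm, and 385 / 0.75 = 514. The stated 500 is within 3% of this. With 500 × 0.75 = 375 followed per arm, power is 78.7%. I therefore use 375 followed, which gives about 188 DMPA-IM and 225 DMPA-SC continuers at 12 months.

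**Assumption not in the document.** The strength of the link between experience and continuation is not given, so a range is shown. Experience among starters is set equal in both arms, so any difference among continuers is spurious.

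**Continuous item.** Let experience be Y ~ N(0,1) in both arms, with correlation ρ to a latent tendency to continue. With continuation proportion p and c the 1−p normal quantile:

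- mean of Y among continuers = ρλ, where λ = φ(c)/p
- variance = 1 + ρ²(cλ − λ²)
- λ = 0.798 at p = 0.50 and 0.644 at p = 0.60, so the spurious difference is −0.154ρ (DMPA-SC minus DMPA-IM)

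| ρ (both arms) | Difference, SD | SE | False-positive rate of a 5% test |
|---|---|---|---|
| 0 | 0 | – | 5% |
| 0.3 | −0.046 | 0.096 | 7.7% |
| 0.5 | −0.077 | 0.091 | 13.5% |
| 0.7 | −0.108 | 0.083 | 25.6% |

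With 50% against 70% continuation, the rates for ρ = 0.3, 0.5 and 0.7 are 16%, 40% and 74%. With equal continuation of 50% but ρ = 0.5 in DMPA-IM and 0.3 in DMPA-SC, the rate is 37%. With equal continuation and equal ρ it stays at 5%.

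**Binary item.** Assume 40% of starters in each arm have a poor experience, and DMPA-IM continuation is 30% (poor) and 63.3% (good): 0.4 × 0.30 + 0.6 × 0.633 = 0.50. The odds ratio is (0.633/0.367)/(0.30/0.70) = 4.0.

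- *Same odds ratio in DMPA-SC, 60% overall.* Continuation is 40.3% (poor) and 73.1% (good). Poor experience among continuers is 0.4 × 0.30/0.50 = 24.0% for DMPA-IM and 0.4 × 0.403/0.60 = 26.9% for DMPA-SC. The gap is 2.9 points (z = 0.67, p ≈ 0.51 with 188 and 225). Repeating this with common odds ratios of 2, 8, 16 and 100 gives gaps of 1.6, 3.8, 4.4 and 4.2 points.
- *Weaker link in DMPA-SC (odds ratio 2).* Continuation is 50% (poor) and 66.7% (good), still 60% overall. Poor experience among DMPA-SC continuers is 0.4 × 0.50/0.60 = 33.3% against 24.0%. The gap is 9.3 points (z = 2.08, p = 0.038).

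**Interview #2.** If losses accrue evenly over three reinjections (assumption), 0.50^(1/3) = 79% and 0.60^(1/3) = 84% reach the experience questions. With the common odds ratio of 4.0 the gap is 33.1% against 34.8%, or 1.7 points (p ≈ 0.66). In the latent model the false-positive rate is about 6%, 8% and 11% for ρ = 0.3, 0.5 and 0.7.

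**The case against.** The strongest reply has four parts.

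1. **Intake reaches everyone.** Enrollment follows receipt of the method, so Tool A can record counseling, training and first-injection experience for all starters before any selection. This stands: those experiences are outside the point. Intake within two weeks cannot, however, capture later side effects or reinjection.
2. **The instruments are not shown.** The discontinuation questions in Additional file 2 may cover side effects, satisfaction or access. This also stands, and it limits how firmly the gap can be stated. The article nevertheless describes the two sets of questions as separate branches, and a later analysis plan cannot recover items that were never asked.
3. **Some items apply only to women who reinjected**, such as help sought with the latest injection. For these, reinjectors are the right denominator.
4. **The effect may be small.** With a common link and the planned 10-point difference it is modest, and smaller still at interview #2.

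A reader might go further and infer that every planned comparison of experiences is invalid, or that a false difference of about 9 points should be expected. The document supports neither. Intake data escape the selection, and the 9-point result needs a much weaker link in DMPA-SC than in DMPA-IM. Self-injection supplies kept at home make such a difference conceivable, but no passage establishes it.

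**Conclusion.** The point holds for follow-up experiences. The plan names enrolled women as the population, but its interview routing yields comparable follow-up data only for women who report another injection, and neither the Data analysis section nor the Discussion says so. A stated rule causes this, not a detail left for later.

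Under the plan's 50% against 60%, with equal true experience and the same link in both arms, the bias is about 0.05 to 0.11 SD, or about 3 points on a 40% item. The false-positive rate is about 8% to 26% for assumed correlations of 0.3 to 0.7. If experience is unrelated to continuation there is no bias. A wider continuation gap or an arm-specific link makes it larger; about 9 points arises here only when the link differs by arm. This is a secondary objective, and the correction is worth making because it is cheap.

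**What to change.** - Put a short common set of items that apply to any starter (satisfaction, side effects, access) to every woman reached, before asking about reinjection and routing on the answer.
- Make the interview #2 comparison, over all women reached, the main arm comparison of follow-up experiences.
- Keep reinjection-specific items among reinjectors and say so.
- Label the interview #3 and #4 comparisons as conditional on earlier continuation, with denominators by arm.

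Enrollment was scheduled for January to June 2024 and interview #2 falls 120–130 days later, so on that schedule the last of these would be due by about early November 2024. Where interviews are already complete, restate the comparison as one among continuers, not enrolled women, and present it beside intake experiences and discontinuation reasons by arm.

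The cost is a few more minutes in an interview that the discontinuer is already giving, a reordering of Tool B where that is still possible, and a narrower stated conclusion. No new contacts are needed. The change does not deal with women who cannot be reached, who remain missing.
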